### Primary outcome

The primary outcome is the difference in uptake (eg, the percentage of eligible people that signed the online informed consent form and completed a risk assessment of the total number of eligible people) between the active and passive recruitment strategy. The total number of eligible people in each recruitment group (active vs passive) are based on the number of new cases of AD or VD in all memory clinics during the recruitment period, assuming an average of one child per patient with dementia receiving the envelope with the PIF including a login access number. Due to privacy regulations, it is not possible to collect data regarding the reasons for non-participation.

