Patients with AD or VD (or their caregivers) receive an envelope either at the registration desk of the memory clinic or after the consult of the patient (only with active recruitment). This envelope is addressed to the middle-aged descendants of patients with recently diagnosed AD or VD and includes a patient information form (PIF) with information about the content of the study, the advantages and disadvantages of study participation and how potential participants can participate. Potential participants (one family member per patient) are asked to register themselves (eg, making an account) on the Demin website (www.demin.nl), by using the memory clinic specific login access code, which is reported on the front page of the PIF and represents the memory clinic in which the parent was diagnosed. The decision to participate is confirmed by the participants by signing the online informed consent form (electronic signature by using SMS-tan). After signing this form, individuals from both recruitment strategies are able to log in to their personalised website ‘My Demin’ and continue the intervention in an equal manner. The personalised website ‘My Demin’ is secured and only accessible for the participant by logging in with their personal email address, password and SMS-tan code. ‘My Demin’ contains the following information: (1) My personal (account) information, (2) Message inbox, (3) My online questionnaires, and (4) My personal health profile including online tailor-made lifestyle advice. After participants have completed the online questionnaire, they automatically receive a message with a request to make an appointment for physical examination including a fasting blood sample. Moreover, participants can invite siblings to participate in the study in ‘My Demin’.

The functionalities provided by the Demin website are based on the literature and input we received from people with a parent with dementia (focus group discussions).

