### Randomisation of memory clinics

To prevent contamination between the two recruitment strategies, randomisation is performed at the level of the memory clinics. To enhance comparability between the intervention (participants of the active recruitment strategy) and control group (participants of the passive recruitment strategy), the memory clinics will be matched and randomised by a statistician, who is blind to the identity of the memory clinics and not involved in the study. First, all participating memory clinics will be matched into pairs based on the following criteria: (1) number of newly diagnosed dementia (VD, AD or mixed dementia) patients seen per year (range vary from 60 to 350 patients per year) and (2) the average social economic position (SEP) of the population living around the memory clinic (neighbourhood SEP), based on data from Statistics Netherlands.^44^ Second, the matched memory clinics will be randomised (pairwise randomisation) to an active recruitment strategy or passive recruitment strategy using a computer-generated random number list. As we expect a higher response rate in the active recruitment strategy group, we use an active:passive recruitment strategy ratio of 8:13 (see sample size calculations).

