### Study population

Eligible participants are middle-aged individuals (40–60 years old) with a parent who is recently (less than 6 months ago) diagnosed with AD or VD (or mixed dementia) at one of the participating memory clinics in the Netherlands (see Acknowledgements section). Individuals should provide informed consent, be able to fill out an online Dutch questionnaire. Pregnant women are excluded from participation.

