### Sample size calculations

The primary outcome measure is uptake, which is defined as the percentage of eligible individuals that signed the online informed consent form and completed baseline assessment (online questionnaire and physical examination and a fasting blood sample). In order to detect a difference of 20% in uptake between the passive and active recruitment strategy (30% vs 50%), we need 94 participants in each group to achieve a power of 80% with alpha levels of 0.05 (total=188 participants). To take cluster randomisation into account, we use the formula 1+((n−1)*ICC) (inflation factor), where n is the average number of included participants per memory clinic and ICC is Intra Class Correlation.^45^ The ICC is unknown, but an ICC of 0.05 is a common value for cluster RCTs in hospitals.^46^ The estimated average of included participants per memory clinic per year is n=15 using a passive recruitment strategy and n=25 using an active recruitment strategy, taking into account non-response. With unequal cluster sizes, ‘n’ is replaced by ‘m’, where m is the sum of (M)^2^/sum(M) ((15^2^+25^2^)/(15+25)).^47^ This results in a sample size inflation factor of (1+((21.25–1)*0.05)=2.01. Therefore, the total number of participants needed is 378 (2.01*188). In order to recruit 378 participants, we need 21 memory clinics, of which eight memory clinics (responsible for 189 included participants) will be allocated to the active recruitment strategy and 13 memory clinics (responsible for 189 included participants) will be allocated to the passive recruitment strategy.

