### Outcome measures and measurements

Participants are invited to fill in the online questionnaire at baseline and four times (3, 6, 9 and 12 months after baseline measurement) during 1 year follow-up. Physical examination, including the fasting blood sample for direct laboratory measurements, is only done at baseline and 12 months after baseline measurement (see online supplemental file 2). Data from the online questionnaires and physical examination are stored automatically in an electronic case report form (eCRF) data management programme, which is only accessible by the researchers involved in this study. Data from the direct laboratory measurement are entered manually in the eCRF data management programme. Every month, memory clinics are requested to provide information about (1) the number of eligible participants (eg, new cases of AD and VD), (2) the number of envelopes that are given away and (3) any difficulties with the recruitment of participants. In order to keep participating memory clinics involved in the study, every 3 months newsletters are sent around and memory clinics are contacted monthly to evaluate the uptake.

10.1136/bmjopen-2020-039439.supp2Supplementary data

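### Uptake is defined among eligible people but divided by all new AD or VD diagnoses, and the planned 30% and 50% are not on that scale

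*Protocol article*

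**What the plan says.** Sample size calculations describes uptake as "defined as the percentage of eligible individuals that signed the online informed consent form and completed baseline assessment", and the planned contrast is 30% (passive) against 50% (active). Study population sets the eligibility rule: "Eligible participants are middle-aged individuals (40–60 years old) with a parent who is recently" diagnosed with AD or VD (or mixed dementia).

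Primary outcome then obtains the denominator differently. The totals of eligible people "are based on the number of new cases of AD or VD in all memory clinics during the recruitment period". The step from patients to eligible people is a stated assumption, worded as "assuming an average of one child per patient with dementia receiving the envelope with the PIF including a login access number". The monthly clinic report in Outcome measures and measurements makes the same equation, asking for "the number of eligible participants (eg, new cases of AD and VD").

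Three other statements bear on the point:
- Study setting and design: "Potential participants (one family member per patient) are asked to register themselves". The same section later lets participants invite siblings, without saying whether siblings count towards uptake.
- Randomisation of memory clinics gives the clinics' annual number of newly diagnosed patients (AD, VD or mixed): "range vary from 60 to 350 patients per year".
- Sample size calculations: "The estimated average of included participants per memory clinic per year is n=15 using a passive recruitment strategy", and 25 using the active strategy.

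**The concern.** A new diagnosis produces an eligible person only if the patient has a child in the age window. Patients with no children, or whose children are all younger than 40 or older than 60, produce none, yet each adds one to the denominator. The article neither excludes these patients nor says how many there are.

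Two things are at stake. First, the 20-point difference used for the sample size is stated among eligible people, whereas the measured quantity is per diagnosis, so the planned effect and the outcome are on different scales. Second, the Introduction says the study will show whether potential participants are willing to take part. On this denominator some of the non-uptake is ineligibility. The article also says that reasons for non-participation cannot be collected, so the two could not be separated afterwards.

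**Working it through.** **1. The plan's own sample size.** Inputs from Sample size calculations: 30% vs 50%, power 80%, alpha 0.05 (two-sided assumed), ICC 0.05, 15 and 25 participants per clinic.
- Per group: 2 × 0.40 × 0.60 × (1.960 + 0.842)² / 0.20² = 94.2, against the stated 94. The version with separate null and alternative variances gives 93.
- Average cluster size: (15² + 25²)/(15 + 25) = 21.25.
- Inflation: 1 + 20.25 × 0.05 = 2.0125.
- Total: 188 × 2.0125 = 378.4, against the stated 378.

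The stated figures reproduce. The question is what the 30% and 50% are percentages of.

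**2. Effect of the eligibility rule.** Let f be the fraction of new patients with at least one eligible child. The documents give no value, so f is an assumption here. With at most one participant per patient:

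uptake per diagnosis = f × uptake among eligible people.

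| f (assumed) | Passive | Active | Difference | Ratio |
|---|---|---|---|---|
| 1.0 | 30% | 50% | 20 points | 0.60 |
| 0.9 | 27% | 45% | 18 points | 0.60 |
| 0.8 | 24% | 40% | 16 points | 0.60 |
| 0.6 | 18% | 30% | 12 points | 0.60 |
| 0.5 | 15% | 25% | 10 points | 0.60 |

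The difference is 20f points. The ratio does not change when f is the same in both arms.

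**3. The planning figures against the stated clinic volumes.**
- Passive: 15 / 0.30 = 50 eligible people per clinic-year.
- Active: 25 / 0.50 = 50 eligible people per clinic-year.
- Stated new patients per clinic-year: 60 to 350, so the average cannot be below 60.
- With an average of 60: 15/60 = 25.0% and 25/60 = 41.7%, a difference of 16.7 points.

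A larger average volume gives lower percentages for the same planned recruitment. The article does not state the average, so 25% vs 42% is the most favourable case.

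**4. Effect on power.** Take 13 and 8 equal-sized clinics, each with 50 eligible people and hence 50/f diagnoses. Use design effect 1 + (50/f − 1) × 0.05 and a two-sided normal approximation.

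| f (assumed) | Diagnoses per clinic | Design effect | Power |
|---|---|---|---|
| 1.0 | 50 | 3.45 | 94% |
| 0.8 | 62.5 | 4.075 | 86% |
| 0.6 | 83.3 | 5.12 | 72.5% |
| 0.5 | 100 | 5.95 | 64% |

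The units here are the people or diagnoses in the denominator (21 × 50 = 1,050 at f = 1). The plan counts its 378 as included participants, which is why the first row exceeds 80%. Extra diagnoses do not restore the lost difference, because at a fixed ICC the design effect grows almost as fast as the denominator. The ICC may itself differ on the per-diagnosis scale.

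**The case against.** The strongest reply is that the assumption is stated openly as an average, that clinics are matched and randomised, and that a count of diagnoses is objective and equally available in both arms. Much of this stands.

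- A reader might infer that 30% vs 50% could never be observed. That does not follow. With one participant per patient it would require true uptake of 30/f% and 50/f% among eligible people, for example 37.5% vs 62.5% at f = 0.8. It is impossible only if f is below 0.5, and f is not given.
- A reader might infer that uptake is certainly understated. That holds under the one-per-patient rule. If invited siblings enter the numerator, families with several participants could offset families with none, and the direction is open.
- A reader might infer a biased comparison between arms. Allocation is random within matched clinics, so a difference in f between arms would be chance. It adds noise, more so with only 8 and 13 clinics, but is not systematic bias.
- Dividing 15 and 25 by 350 would apply average recruitment to the largest clinic, which nobody planned. Only an average volume may be used, and only its lower bound follows from the documents.
- The 60 to 350 range includes mixed dementia, which Primary outcome does not name. If mixed cases are not counted, the relevant volumes are smaller and the gap in step 3 narrows.
- Asking every new patient about children could itself prompt recruitment in passive clinics, or be done more thoroughly in active ones. Replacing the denominator is therefore not free of risk.

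What the reply does not remove is the mismatch itself. Disclosing an average of one child does not exclude patients without a child aged 40–60, and it does not place 30% and 50% on the per-diagnosis scale.

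**Conclusion.** The concern holds in a limited form. The primary outcome is labelled as uptake among eligible people but is measured per new diagnosis, and the rates that drive the sample size belong to the former. Under one participant per patient, absolute uptake and the absolute difference shrink by the factor f, to 24% vs 40% at an assumed f of 0.8 and to 18% vs 30% at 0.6. The relative comparison of the two strategies survives if f is similar across arms.

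Independently of f, the planned 15 and 25 per clinic-year correspond to at most 25% vs 42% on the stated clinic volumes, provided that the 60 to 350 range describes the cases counted in the denominator. Loss of power depends on f and on the actual volumes. Under the simplifications shown, it falls from 94% at f = 1 to 86% at 0.8 and 64% at 0.5.

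**What to change.** Define the primary outcome as participating families per new AD or VD diagnosis: one index participant per patient in the numerator, invited siblings excluded, and an explicit statement of whether mixed dementia is counted. Restate the expected rates, the difference and the power on that scale, using the clinics' actual new-case counts. Do not interpret the result as willingness among eligible people.

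Where clinics can record whether a new patient has a child aged 40–60, in the same way in both arms and without prompting recruitment in passive clinics, report uptake on that denominator as well. Otherwise give a sensitivity analysis over a stated range of f, including modest differences between arms.

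The redefinition needs no new data and no extra participants. The cost is less favourable stated percentages and possibly lower stated power. The optional recording adds clinic work and carries the contamination risk noted above, so it should supplement the per-diagnosis outcome and not replace it.

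### Siblings invited by participants can enter the uptake numerator, while the denominator allows an average of one child per new case

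*Protocol article*

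**What the plan says.** All references are to the protocol article.

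- **Numerator.** Primary outcome defines uptake as "the percentage of eligible people that signed the online informed consent form and completed a risk assessment", out of all eligible people. Sample size calculations gives the same definition and spells out the baseline assessment.
- **Denominator.** The same section says that the totals of eligible people "are based on the number of new cases of AD or VD in all memory clinics during the recruitment period". It moves from a count of cases to a count of people by "assuming an average of one child per patient with dementia receiving the envelope".
- **Who registers.** Study setting and design says: "Potential participants (one family member per patient) are asked to register themselves". They use an access code that is specific to the memory clinic.
- **Siblings.** The same section later adds that "participants can invite siblings to participate in the study in" the personal My Demin area. It does not say how siblings are treated in the uptake count.
- **Eligibility.** Study population requires a parent recently "diagnosed with AD or VD (or mixed dementia) at one of the participating memory clinics". Randomisation of memory clinics also counts mixed dementia when matching clinics. The monthly clinic count (Outcome measures and measurements) and the Primary outcome section name only AD and VD.
- **Analysis.** Statistical analyses specifies multilevel logistic regression with clustering at clinic level.

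**The concern.** The two halves of the primary outcome can count different units. The denominator grows by one, on average, for each diagnosed patient. The numerator grows by one for each eligible person who completes baseline. A sibling aged 40–60 of an eligible child has the same diagnosed parent and can meet the same eligibility rule, and the article itself opens a route by which that sibling can join.

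Siblings who come in by invitation do so through someone already recruited, so the effect multiplies each arm's own uptake rather than adding a constant. The primary outcome is a difference, so even an equal sibling rate in both arms changes it. Unequal rates change the ratio of uptakes as well. Logistic regression also needs each success to be one of the persons at risk, and a second or third child of the same patient is not in a count of one per case.

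The information has to be captured prospectively. The access code identifies the clinic and not the patient, so the code alone cannot later show which participants share a parent.

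**Working it through.** **1. The plan's own figure.** Inputs from Sample size calculations: uptake 30% passive and 50% active, power 80%, alpha 0.05 (two-sided assumed), ICC 0.05, 15 and 25 participants per clinic per year.

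- Two proportions, pooled variance: n = [1.96 × √(2 × 0.4 × 0.6) + 0.842 × √(0.3 × 0.7 + 0.5 × 0.5)]² / 0.20² ≈ 93 per arm. The plan has 94, which is close enough.
- m = (15² + 25²)/(15 + 25) = 21.25.
- Inflation factor = 1 + (21.25 − 1) × 0.05 = 2.0125.
- 188 × 2.0125 = 378.35. The plan has 378.

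The sample size reproduces. It rests on 50% vs 30%, which fits one index child per case, so a one-child rule leaves it at 378.

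**2. Effect of siblings.** Let p be the share of cases with a joining family and s the extra siblings per joining family who complete baseline. Then recorded uptake = p × (1 + s). The article gives no value for s, so 0.1 to 0.4 is an assumed range.

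- Active: 50 × 1.1 = 55% to 50 × 1.4 = 70%.
- Passive: 30 × 1.1 = 33% to 30 × 1.4 = 42%.

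| s active | s passive | Active | Passive | Difference |
|---|---|---|---|---|
| 0 | 0 | 50% | 30% | 20 points |
| 0.2 | 0.2 | 60% | 36% | 24 points |
| 0.1 | 0.3 | 55% | 39% | 16 points |
| 0.3 | 0.1 | 65% | 33% | 32 points |

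With equal s the ratio of uptakes stays at 50/30 = 60/36 = 1.67, but the difference stretches by the factor 1 + s.

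**3. No true difference.** With equal true uptake and equal s, no false difference is expected. With s = 0.25 in one arm only, true uptake of 30% in both arms gives 37.5% vs 30%, a false 7.5 points. True uptake of 50% in both arms gives 62.5% vs 50%, a false 12.5 points.

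**4. Could uptake pass 100%?** Through siblings alone, this needs s > 1/0.5 − 1 = 1.0 in the active arm or s > 1/0.3 − 1 = 2.33 in the passive arm. As a cross-check, take the lowest caseload given for clinic matching, 60 new patients per clinic per year, and assume one year of recruitment. The planned 189 participants per arm are then 189/(8 × 60) = 39% of cases (active) and 189/(13 × 60) = 24% (passive).

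**5. Mixed dementia.** If a share x of eligible cases is mixed and left out of the denominator, recorded uptake = p/(1 − x). An assumed x of 0.1 gives 55.6% vs 33.3%, and 0.2 gives 62.5% vs 37.5%. The article does not give x, and x is zero if mixed cases are counted.

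**The case against.** The best defence is that the sections can be read together. Uptake is written as a proportion of the eligible people. Those people are tied to one child per patient receiving the envelope, and the registration sentence also speaks of one family member per patient. Invited siblings would then be extra participants outside the uptake count, with the counting rule left to the full protocol or SAP. That reading is possible, and it would make the two sentences about families compatible. But the article defines both counts itself, its numerator has no such restriction, and no sentence takes siblings out. The ambiguity therefore stands.

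A reader might infer several stronger claims, which the article does not support:

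- **Uptake is biased upward.** Siblings push it up, but patients with no child aged 40–60 stay in the denominator and push it down. The article says openly that one child is an assumed average. The net direction is unknown.
- **Uptake may exceed 100%.** This is arithmetically possible but remote, as step 4 shows.
- **Mixed dementia is left out of the denominator.** The Introduction describes mixed dementia as a combination of AD and VD, so naming only those two may be shorthand. The conflict is one of wording.
- **The diagnosis windows distort the result.** A parent diagnosed within the 6 months before recruitment opened makes a child eligible without being a new case in the period. Late diagnoses may work the other way. This is an edge effect that cannot be sized.
- **The logistic model is invalid.** Extra between-clinic variation caused by siblings would largely enter the clinic-level variance. The model does not, however, restore a denominator that omits the siblings.

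The article also gives no figure for unequal sibling rates. The Introduction suggests that passive recruits may be more intrinsically motivated, which makes a difference plausible but does not show one.

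**Conclusion.** The point holds as a mismatch of units in the primary outcome. As written, invited siblings can be counted as uptake without being counted as eligible. The size depends on s, which is an assumption throughout. For s of 0.1 to 0.4, the planned 50% vs 30% reads 55–70% vs 33–42%. In the scenarios tabulated, the difference ranges from 16 to 32 points against a target of 20. The shift is material if sibling participation is appreciable and vanishes if s is zero.

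The documents do not show that absolute uptake is biased in a given direction, that the arms will differ in s, or that mixed cases are in fact omitted. The diagnosis wording and the diagnosis window are supporting clarifications. The planned sample size is not in question.

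**What to change.** - In Primary outcome, state that the uptake numerator counts at most one index descendant per diagnosed patient.
- At registration, record whether the person joined through a sibling invitation or has a sibling already enrolled. A flag on invitations alone would miss siblings who register directly with the clinic code, and that code cannot show that two people share a parent.
- Exclude such siblings from primary uptake and report their number by arm. Keep them in the secondary analyses with a family level, which requires that siblings be linked to each other and not only flagged.
- Name AD, VD and mixed dementia consistently in the monthly clinic count and in Primary outcome, to match the eligibility and matching criteria.
- State one diagnosis window that applies to both numerator and denominator.

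The cost is one extra registration item, clearer wording on the clinics' monthly count and a slightly lower headline uptake. The sample size stays at 378.
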